Patient participants will be identified using an automated practice database search strategy designed by the research team. The practice administrative team will use this ‘flag’ to identify ten consecutive potential participants with pre-booked consultations with each of the three recruited GPs. Random sampling of participants is not required as the clinical presentations, and therefore the nature of the decision-making between consecutive consultations, is expected to be random. A total of 180 (minimum 120) potential patients will be identified across 6 practices, with the aim of recruiting at least half.

The sample size is sufficient to compare between-group differences in quantitative feasibility objectives such as recruitment rates and data collection procedures including the completeness of participant questionnaires. This sample size also allows the estimation of standard deviations for the clinical outcome measures being tested. In addition, it is sufficient to obtain a purposively selected sub-sample of participants for process evaluation interviews, to achieve the qualitative feasibility objectives.

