### Recruitment procedures

Non-compliance with the intervention will be taken into account at patient, GP or practice level by over-recruiting. Practices will receive email and phone correspondence inviting their participation. Practice recruitment will be dependent on an expression of interest from at least two of their GPs. Practices will be incentivised through payment for local coordination and set-up. GPs will receive a certificate for the training course (Williamson et al. 2007).

For each recruited GP, ten potential patient participants with pre-booked appointments will be screened by GPs, and if eligible, contacted by post ahead of their appointment. They will receive a cover letter, participant information sheet and example consent form. On their arrival in the practice waiting room, the receptionist will provide the patient with a pre-consultation questionnaire.

Patients who do not wish to participate will indicate this with a tick box on the pre-consultation questionnaire. Practices will keep an anonymised log of patients who declined to participate. A tick box on the post-consultation questionnaire will enable patients to opt out of process evaluation interviews and/or from having their case notes reviewed.

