### Analysis

#### Recruitment capability, consent and randomisation procedures, sample characteristics

The trial will determine whether it is possible to recruit appropriate study participants to test the intervention, or whether amendments are required ahead of a future trial. The flow of participants will be summarised in a Consort diagram. Numbers of eligible clusters, individual participants identified and randomised, recruitment rates and attrition will be recorded.

The search strategy used to identify potentially eligible patients will be tested on different practice databases with a view to finalising a generic, universal search algorithm. Anonymised data on ineligible patients will provide a profile of those frequently excluded. Consideration will be given to whether adaptations to the trial could be appropriate, to enable these patients to participate in a future study.

Any difficulties with meeting recruitment targets (6 practices; at least 2 GPs per practice; at least 5 patients per GP) will be documented. Field notes and correspondence with practices will enable the issues to be explored. Patients’ reasons for declining will be reviewed in light of recruitment procedures. For example, patients will use the pre-consultation questionnaire to indicate whether they received the information pack in the post. The extent to which over-recruitment is necessary will be reviewed, as will the importance of incentivising participants.

Randomisation procedures will be discussed at team meetings to inform amendments prior to a larger trial. For example, consideration will be given to randomising more practices to the intervention than to usual care, to gather more data regarding intervention implementation if required. Consideration will be given to initiating the study in each of the three sites sequentially (e.g. inner city, then urban, then rural) in order to increase trial management capacity. Consideration will be given to blinding the research team for data analysis in the future trial.

Rates of patient consent, to the use of questionnaire data, to video-recording ([12]; Asan and Montague 2014) and to case note review, will be evaluated. Numbers lost to follow-up will be reviewed; however, it is anticipated that this will be minimal. The study will determine whether there are differential drop-out or recruitment rates between intervention and control groups (indicative of selection bias).

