### Criteria for progression to a future definitive randomised controlled trial of the intervention

Study processes are designed to be iterative, formative and adaptive [6]. However, there are certain criteria on which progression to a future, larger trial of intervention effectiveness is dependent. These are:
Recruitment
> 80% of general practices approached (i.e. 5/6)> 60% of GPs approached per practice (i.e. 2/3)> 50% of patients approached per practice (i.e. 20/30)Collection of outcomes
> 60% of patient-reported outcomes (questionnaire response rate)> 70% of patient questionnaire respondents providing written consent to case-note review> 70% of video recordings useable for observer ratings

Loss to follow up is expected to be minimal and is therefore not included as a ‘stopping criteria’.

The Chief Investigator, the Trial Steering Committee and the sponsor have the authority to stop or advise modifications to the feasibility trial.

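### The patient-recruitment progression criterion contradicts itself: more than 50% of 30 is at least 16, but the count given as its equivalent, 20/30, is 66.7%

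*Protocol article*

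**What the plan says.** Under the heading on criteria for progression, the protocol article first calls the study processes adaptive. It then states that "there are certain criteria on which progression to a future, larger trial of intervention effectiveness is dependent". Three recruitment criteria follow, each a strict inequality (more than) on a percentage, with a count in brackets introduced by i.e.:

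- practices: more than "80% of general practices approached (i.e. 5/6")
- GPs: more than "60% of GPs approached per practice (i.e. 2/3")
- patients: more than "50% of patients approached per practice (i.e. 20/30")

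The 30 in the patient criterion comes from the Sampling section, where the practice identifies "ten consecutive potential participants with pre-booked consultations with each of the three recruited GPs", so 3 × 10 = 30. That section also gives the recruitment intention for the patients identified: "with the aim of recruiting at least half". The analysis section on recruitment capability repeats the target per GP: "Any difficulties with meeting recruitment targets (6 practices; at least 2 GPs per practice; at least 5 patients per GP) will be documented".

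**The concern.** The bracketed count is offered as a restatement of the percentage, but it describes a much higher bar. Progression is a main output of a feasibility trial, and this criterion is one of those on which it is said to depend. If a practice's recruitment falls between the two bars, the same data support a pass or a fail according to which half of the line is read. That choice would be made after the data are known. There is also a mismatch at the boundary: the recruitment aims are worded as at least half, but the criterion is worded as more than half.

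**Working it through.** **Inputs.** Thresholds and bracketed counts come from the progression criteria. The 30 patients per practice (three GPs, ten patients each) and the aim of at least half come from Sampling. The target of at least five patients per GP comes from the recruitment capability section.

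**Step 1: reproduce the bracketed counts.** For each criterion, find the smallest whole number k with k/n strictly above the stated percentage.

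| Criterion | n | Threshold | Smallest k | k/n | Count in the article | Agrees? |
|---|---|---|---|---|---|---|
| Practices | 6 | > 80% | 5 | 83.3% | 5/6 | yes |
| GPs | 3 | > 60% | 2 | 66.7% | 2/3 | yes |
| Patients | 30 | > 50% | 16 | 53.3% | 20/30 = 66.7% | no, 4 patients too many |

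The first two counts are exact minimum counts, so the third cannot easily be taken as a loose illustration of a value above the bar.

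**Step 2: try other readings.** At least 50% of 30 gives 15. More than 50% of 20 (two GPs) gives 11. A count of 20 is the minimum above 50% only when 38 or 39 patients are approached (20/38 = 52.6%, 20/39 = 51.3%; with 40, 20 is exactly 50%). No reading gives 20/30.

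**Step 3: the disputed band.** With 30 approached, 16 to 19 recruits (53.3% to 63.3%) pass on the percentage and fail on the count.

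**Step 4: how often a practice would fall there.** The article gives no uptake rate, so the rates below are assumptions. With X the number recruited of 30, binomial and independent between patients, the band has probability P(X ≥ 16) − P(X ≥ 20). Differences were taken before rounding.

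| Assumed uptake | P(X ≥ 16) | P(X ≥ 20) | P(16 to 19) |
|---|---|---|---|
| 40% | 0.10 | 0.00 | 0.09 |
| 50% | 0.43 | 0.05 | 0.38 |
| 60% | 0.82 | 0.29 | 0.53 |
| 65% | 0.93 | 0.51 | 0.43 |
| 70% | 0.98 | 0.73 | 0.25 |
| 80% | 1.00 | 0.97 | 0.03 |

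**Step 5: the boundary at exactly half.** Five of ten for each of three GPs is 15/30 = 50.0%. That meets at least half but not more than half. If all 30 are approached, P(X = 15) is 0.14 at 50% uptake and 0.08 at 60%.

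**The case against.** The best defence is that the intention is easy to guess. Both recruitment aims point to about half, so the percentage is probably meant and 20/30 is probably a slip. The criterion is one of six, the study is described as adaptive, and no estimate or participant's safety depends on it. The disagreement also matters little at low or high uptake. All of this is fair and limits the weight of the point. It does not remove it, because the sentence that introduces the criteria makes progression depend on them, and the article does not say which figure governs.

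Four stronger conclusions are tempting but not supported.

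- *A trial that exactly meets its recruitment target must fail the criterion on the percentage.* The denominators differ. The aim of at least half refers to patients identified; the criterion refers to patients approached. Under Recruitment procedures, GPs screen the ten and only those eligible are contacted. If one is screened out, five recruits are 5/9 = 56% of those approached, which passes on the percentage. The conflict at exactly half arises only if nobody is screened out.
- *The GP criterion cannot fail.* A reader might infer this from "Practice recruitment will be dependent on an expression of interest from at least two of their GPs". But the article does not cap the number of GPs approached at three: two of four is 50% and fails. An expression of interest is also not written consent.
- *A two-GP practice would need 20 of 20.* The bracket is a fraction for a three-GP practice. Nothing carries the count of 20 over to a smaller denominator.
- *The criterion should be judged on all 180 patients together.* It is stated per practice, and the error gives no reason to change that.

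**Conclusion.** The point holds as an internal contradiction in one decision threshold. As written, the patient criterion sets two bars, 16/30 and 20/30, which are four patients apart. That follows from arithmetic on the article's own figures and needs no assumption. Its practical size depends on uptake. The two readings disagree for a practice of 30 with probability between 0.25 and 0.53 at the tabulated rates from 50% to 70%, and below 0.10 at 40% and at 80%. These probabilities assume that all 30 are approached and that patients respond independently; clustering by GP or practice would change them. The strict inequality at exactly half is a secondary wording matter.

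**What to change.** Before data are seen, state one patient-recruitment threshold in which the percentage, the inequality and the count say the same thing, and keep it per practice.

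- To agree with the Sampling and recruitment capability sections: at least 50% of patients approached per practice, i.e. 15/30, or 10/20 where two GPs take part. This also settles the boundary at exactly half.
- If two thirds was intended: at least two thirds of patients approached per practice, i.e. 20/30, with the aims in those two sections raised to match. It is safer to write the fraction than a rounded 67%, because 0.67 × 30 = 20.1 and a literal 67% would exclude 20/30.

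It would help to add that the counts assume all ten patients per GP are approached, and that the percentage applies when screening reduces that number. The cost is a wording change agreed with the Trial Steering Committee; under the first option, sample size, data collection and analysis stay as they are.

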### Sampling

Six GP practices will be recruited from rural Devon and from each of the cities of Exeter and Plymouth, UK. A minimum practice size of 3000 patients will ensure sufficient numbers of eligible participants. (It is anticipated that there will be approximately 800 older patients with multimorbidity in an average 8000 patient practice [1]). Table 1 shows the participant inclusion and exclusion criteria. An average of three (total = 18 GPs), and at least 2, GPs per practice will be recruited. Patients aged 65 and above with known multimorbidity, defined as the presence of two or more long-term conditions (as specified in Table 1), will be approached.

**Table 1 Tab1:** Participant inclusion and exclusion criteria

Participant type	Inclusion criteria	Exclusion criteria
GPs	Only permanent GPs (partners and salaried) to avoid loss to follow-up.	Locum (sessional) GPs Trainee GPs (GPs will not be excluded based on less than full time working)
Patients	Patients aged 65 and above with known multimorbidity The condition should be one of^a^: angina or long-term heart problem; arthritis or long-term joint problem; asthma or long-term chest problem; blindness or severe visual impairment; cancer in the last five years; deafness or severe hearing impairment; diabetes; epilepsy; high blood pressure; kidney or liver disease; long-term back problem; long-term mental health problem; long-term neurological problem.	Temporary residents and vulnerable patients e.g. those recently bereaved, those with severe mental illness, severe cognitive impairment, end stage disease, communication difficulties e.g. physical impairment caused by a stroke as opposed to language barriers, a learning disability, or those unable to complete questionnaires or interviews for any other reason. (A minimum time for a condition to be ‘long-term’ will not be specified)

^a^This list was adapted from the English National General Practice Patient Survey [10]. Where dyads of conditions occur within the same organ system, e.g. anxiety and depression, these will only be counted once e.g. mental health problem

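### The progression criterion for the putative primary outcome counts only recordings that were made, so recruited patients who are never recorded are covered by no threshold

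*Protocol article*

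**What the plan says.** The protocol article's section on criteria for progression to a definitive trial lists conditions on which progression depends. For the collection of outcomes there are three:

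- a questionnaire response above 60%;
- more than 70% of those returning a questionnaire agreeing in writing to case-note review;
- more than "70% of video recordings useable for observer ratings".

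The recruitment condition for patients is more than "50% of patients approached per practice (i.e. 20/30").

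Table 4 names the OPTION(5) observer score as the putative primary outcome. The section on preliminary evaluation of participant responses says that these scores come from video-recorded consultations. The section on evaluation of outcome measures restricts the analysis to observed data, without imputation.

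Consent to video is separate from consent to take part. The analysis section on recruitment capability lists, among the things to be evaluated, "Rates of patient consent, to the use of questionnaire data, to video-recording" and to case-note review. Table 3 says that the rates of recordings that are missing, incomplete or not usable will be reported, and it considers prompting GPs to start the camera. Neither place sets a threshold.

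**The concern.** A consultation that was never filmed is not a recording, so it is in neither the numerator nor the denominator of the video criterion. The criterion therefore tests the technical quality of the films that exist. It does not test whether the outcome can be obtained from the patients who join.

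The protocol itself treats refusal of video and recordings not made as possible events, since it plans to describe both. It also sets a consent threshold for case-note review, which supplies additional outcomes, but none for video, which supplies the intended primary outcome.

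Two things are at stake. All listed criteria could be met while the primary outcome is absent for most recruited patients, so the rule would not show that a definitive trial can collect it. And the feasibility trial is meant to estimate the standard deviation of this outcome in each arm, which becomes imprecise if few consultations are filmed.

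**Working it through.** **Inputs.**
- Patients identified: "A total of 180 (minimum 120) potential patients will be identified across 6 practices, with the aim of recruiting at least half" (Sampling). With ten patients per GP, 6 × 3 × 10 = 180 and 6 × 2 × 10 = 120, so the protocol's figures reproduce.
- Patient criterion: above 50% in each practice, illustrated as 20/30.
- Video criterion: above 70% of recordings.
- v, the share of recruited patients with a recording: not given. Assumed range 20% to 100%.

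**Number recruited when the patient criterion is met.** The protocol's illustration, 20/30 = 66.7%, gives 6 × 20 = 120 over six practices. The smallest count above 50% is 16/30 = 53.3%, which gives 6 × 16 = 96. I use both.

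**Outcome available at the pass mark.** Recordings made = v × recruited. The criterion needs just over 0.70 of these, so

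share of recruited patients with the outcome ≈ 0.70 × v.

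This share is below one half when v < 0.50 / 0.70 = 71.4%.

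**Smallest whole number of usable videos strictly above 70% of recordings:**

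| Recruited | v | Recordings | Usable needed | Share of recruited |
|---|---|---|---|---|
| 120 | 100% | 120 | 85 | 70.8% |
| 120 | 80% | 96 | 68 | 56.7% |
| 120 | 70% | 84 | 59 | 49.2% |
| 120 | 50% | 60 | 43 | 35.8% |
| 120 | 20% | 24 | 17 | 14.2% |
| 96 | 100% | 96 | 68 | 70.8% |
| 96 | 70% | 67 | 47 | 49.0% |
| 96 | 40% | 38 | 27 | 28.1% |
| 96 | 20% | 19 | 14 | 14.6% |

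Every row passes the video criterion, and no other listed criterion changes with v.

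**Effect on the standard deviation.** Ignoring clustering, the upper 95% limit of a standard deviation from n observations is the estimate times √[(n − 1)/χ²], with the 2.5% quantile of chi-squared on n − 1 degrees of freedom.
- 27 usable videos, about 13 per arm: √(12/4.404) = 1.65.
- 68 usable videos (more than 70% of 96 recruited), 34 per arm: √(33/19.05) = 1.32.

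**With recruited patients as the denominator.** More than 70% would need 85 usable videos of 120, or 68 of 96, whatever v is. The outcome could then be missing for at most about 29% of recruited patients.

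**The case against.** The strongest reply is that the failure would be seen. Consent to video is evaluated, missing recordings are reported, reasons for missing outcome data are recorded, and the suitability of each outcome measure for a definitive trial is to be reviewed. The outcome is called putative, and the progression section describes an adaptive process in which meeting the criteria is not said to be sufficient. All this stands. It makes the gap a missing threshold rather than a hidden failure. It does not close the gap: a rate without a threshold does not bind, and deciding what rate is acceptable after seeing it is what criteria set in advance are meant to prevent.

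A second reply is that v may be high. That also stands. Above about 71% recorded, most recruited patients have the outcome at the pass mark, and the protocol offers no figure either way.

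A third is that recordings may mean recordings expected. The wording does not say so, and making it say so is the fix.

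A reader might also infer that the GP criterion has the same defect, because "Practice recruitment will be dependent on an expression of interest from at least two of their GPs" and the criterion is more than "60% of GPs approached per practice (i.e. 2/3"). The protocol does not support that reading. GPs who are approached and decline are in the stated denominator. A practice lost for want of two interested GPs counts against the practice criterion, more than "80% of general practices approached (i.e. 5/6"). The two-GP rule makes the GP criterion automatic only where two or three GPs are approached and interest becomes enrolment; with four approached, 2/4 = 50% fails. The protocol gives the number of GPs to be recruited, not the number approached. The GP criterion also has no bearing on whether the primary outcome is missing.

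**Conclusion.** The point holds for the video criterion. As worded, it can be met at any level of video refusal or failure to record, and no other progression criterion limits these. At the pass mark, the share of recruited patients with the putative primary outcome is about 0.70 × v: 28% with 96 recruited and v = 40%, and 36% with 120 recruited and v = 50%. That the outcome is missing for most patients is conditional on v below about 71%. The values of v are assumptions.

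The conclusion does not extend to the GP criterion. Nor should the Discussion be read as predicting refusal of video: it says that GPs may be hard to recruit and does not mention refusal of recording.

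The change should be made, because the rule otherwise does not test whether the intended primary outcome can be collected. It does not invalidate the feasibility trial, since the rates needed to judge the matter are already to be reported.

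**What to change.** Restate the video criterion as the share of recruited (consented) patients who have a usable recording of the index consultation. Keep the threshold at more than 70%, or fix another before any data are seen; a lower figure can be defended, given that the questionnaire criterion is set at 60%. Report the components beside it: consented to video, recorded, and usable for rating.

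The cost is a line of wording. Video consent and missing or unusable recordings are already to be evaluated or reported, so no new data collection is needed. The downside is that the criterion becomes harder to meet: at 70% with 120 recruited it needs 85 usable videos, where the present wording would accept 43 if half the patients were recorded.

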### Data management, trial monitoring and participant safety

The Data Management Plan and Data Privacy Impact Assessment are included in the Appendix. Monitoring will be carried out by the Trial Steering Committee in conjunction with the Chief Investigator and the supervisory team. Prospective, planned deviations or waivers to the protocol are not allowed under the UK regulations on Clinical Trials and must not be used. Accidental protocol deviations will be adequately documented, reported to the Chief Investigator, sponsor and ethics committee as indicated.

